## Abstract

Adjunctive therapy for hypertension is in high demand for clinical research. Therefore, several meta-analyses have provided sufficient evidence for meditation as an adjunct therapy, without being anchored on reliable physiological grounds. Meditation modulates the autonomic nervous system. Herein, we propose a hierarchical-dependent effect for the carotid body (CB) in attenuating blood pressure (BP) and ventilatory variability (VV) fine-tuning due to known nerve connections between the CB, prefrontal brain, hypothalamus, and solitary tract nucleus. The aim of this exploratory study was to investigate the role of CB in the possible decrease in BP and changes in VV that could occur in response to meditation. This was a prospective, single-center, parallel-group, randomized, controlled clinical trial with concealed allocation. Eligible adult subjects of both sexes with stage 1 hypertension will be randomized into 1 of 2 groups: transcendental meditation or a control group. Subjects will be invited to 3 visits after randomization and 2 additional visits after completing 8 weeks of meditation or waiting-list control. Thus, subjects will undergo BP measurements in normoxia and hyperoxia, VV measurements using the Poincaré method at rest and during exercise, and CB activity measurement in the laboratory. The primary outcome of this study was the detection of changes in BP and CB activity after 8 weeks. Our secondary outcome was the detection of changes in the VV at rest and during exercise. We predict that interactions between hyperoxic deactivation of CB and meditation; Will reduce BP beyond stand-alone intervention or alternatively; Meditation will significantly attenuate the effects of hyperoxia as a stand-alone intervention. In addition, VV can be changed, partially mediated by a reduction in CB activity. Trial registration number: ReBEC registry (RBR-55n74zm). Stage: pre-results.

## 1. Introduction

### 1.1. Background and rationale

Systemic arterial hypertension (HT) was the leading cause of cardiovascular mortality in 2010.^[1]^ Although the latest american college of cardiology & american heart association (2018) guidelines on HT do not recommend meditation,^[1]^ this opinion is not shared by the American Heart Association^[2,3]^ and the International Society of Hypertension.^[4]^ However, the mechanisms underlying these effects are largely unknown.

Meditation can modulate the autonomic nervous system (ANS),^[5–8]^ although a recent meta-analysis did not support this premisse.^[9]^ Herein, we propose a role for the carotid body (CB), the principal oxygen chemoreceptor in humans, playing crucial functions in maintaining respiratory, cardiovascular, and neurohumoral homeostasis.^[10]^ The rationale for this hypothesis is supported by the meaningful nerve connections between the CB, hypothalamic areas, and *nucleus tractus solitarii*,^[11–14]^ with a prevailing effect on increasing sympathetic activity in normoxic conditions due to abnormal hypertonicity in HT.^[12,14]^ In fact, there is some evidence of a link between meditation and balance of neurotransmitters in the hypothalamus.^[15–17]^ We speculate that the connection between meditation, the hypothalamus-pituitary-adrenal axis (HPA), and CB activity would involve stabilization of the HPA axis, as has been proposed with respect to yoga^[18–20]^ or transcedental meditation^[21]^–and a highly coordinated engagement of brain structures such as the prefrontal cortex, amygdala, and hippocampus (hyperachical-dependent activity). Of note, the prefrontal cortex, amygdala, and hippocampus gray matter have been shown to change with yoga/meditation.^[22–25]^ Interestingly, hypertonicity of the CB^[12,26–29]^ and increased size and weight of the CB^[30–35]^ are common findings in HT. However, inconsistent evidence has revealed a decrease in systemic blood pressure (BP) through CB deactivation in response to hyperoxia in hypertensive subjects,^[36–38]^ suggesting that hyperactivity of the CB may be mechanistically associated with sympathetic dysregulation.^[12,39]^ In addition, CB and BP are closely linked to ventilatory variability,^[40–42]^ and lifestyle interventions can reduce ventilatory variability during exercise.^[43]^ Acute changes in breathing variability have also been demonstrated during meditation.^[44]^

### 1.2. Study aims and outcomes

Thus, suspected hyperactivity of CB beyond hypoxic states would be a straightforward pathway to investigate mechanisms underpinning anti-stress therapies in HT, which could theoretically decrease the hierarchical-dependent influence of CB. This exploratory study aimed to investigate the putative role of CB in the decrease in BP and changes in ventilatory variability that could occur in response to meditation. Hence, the primary outcome of this study was to detect changes in BP and CB activity after 8 weeks of meditation. The secondary outcomes were changes in rest and exercise ventilatory variability. We anticipate that interactions between hyperoxic deactivation of CB and meditation at 8 weeks; Will reduce BP beyond stand-alone intervention, or alternatively; Meditation will significantly attenuate the effects of hyperoxia as a stand-alone intervention for BP. In addition, breathing variability could change, partially mediated by a reduction in CB activity.

## 2. Material and Methods

### 2.1. Study design and setting

This was a prospective single-center, parallel-group, randomized, controlled trial with concealed allocation and with 8 weeks of follow-up analyzed using an intention-to-treat approach. The study will be performed at the Laboratory of Respiratory Pathophysiology (LAFIR) at the Respiratory Division of the University Hospital (HUMAP) and the comprehensive care and monitoring of persons with hypertension in primary health care. This will be performed according to the SPIRIT (2013) guideline checklist and recommendations. A Schedule of enrollment, interventions, and assessments from the SPIRIT guidelines is shown in Figure 1.

**Figure 1. F1:**
[figure not shown]
Schedule of enrollment, interventions, and assessments from SPIRIT Guidelines. DASS-21 = Depression, anxiety and Stress Scale, BMQ = Brief medication questionnaire.

### 2.2. Participants’ timeline

This study began in October 2022 and is expected to end after 18 months. The subjects will be invited to 3 visits after randomization and 2 additional visits after completing 8 weeks of a meditation trial. Anthropometric, demographic, and self-report data will be collected on the 1^st^ visit, and familiarization with the laboratory procedures will be performed. In addition, a preparatory briefing will be delivered by a trained researcher who is not involved in the laboratory work. The preparatory briefing consisted of an hour-long talk about HT diagnosis and management. The 2^nd^ visit to the lab will be dedicated to studying resting ventilatory variability (RVV), BP measurements under normoxic or hyperoxic trials conditions (NHT), and resting carotid-body activity (RCBA). The 3^rd^ visit will involve symptom-limited maximal cardiopulmonary exercise testing (CPET) and exercise ventilation variability (EVV) acquisition. The same sequence for the in-lab physiological study will be performed after 8 weeks of meditation or control participation (Fig. 1).

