#### 2.4.4. Randomization and assignment.

Recruitment, randomization, and assignment will be conducted by 4 researchers. Two researchers will be involved in enrolling subjects in the comprehensive care and monitoring of persons with hypertension in primary health care. Another researcher randomized the subjects into 2 parallel groups through block randomization (block size:8) using computer-generated random numbers (random.org). A 4^th^ researcher assigned the participants to 2 groups at an allocation ratio of 1:1. The opaque envelopes enclosing the study group allocation will be numbered consecutively and sealed. Once a patient signs the informed consent form and baseline data acquisition has been concluded, the study researcher will open the envelope with the lowest remaining serial number, and the patient will accordingly be allocated to a group. The subjects will be randomly assigned to 2 groups: a transcendental meditation group and a control group (CG). The CG will remain under pharmacological treatment for 8 weeks and will be set up on a waiting list. Both groups were contacted weekly for adherence and adverse events. The CONSORT flowchart of the participants is shown in Figure 2. A careful explanation of the study’s potential social and academic pertinence and benefits will be provided during the consent action to encourage participant adherence to the intervention and assessments.

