#### 2.5.4. Preparatory briefing about HT and meditation.

On the 1^st^ visit, the subjects allocated to both groups will be invited to an introductory explanation of hypertension after laboratory instrument familiarization. A researcher not directly involved in lab data collection will introduce fundamental knowledge about essential hypertension, the autonomous nervous system, and treatment. The CG will only receive information about hypertension and the meditation group will receive an additional preparatory briefing about meditation during the 1^st^ meditation session.

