#### 2.5.5. Familiarization.

During the 1^st^ visit, all randomized subjects will be invited to the laboratory to perform several normoxic BP measurements using naso-oral masks and accessories under paced breathing. Submaximal testing (up to Borg 5) with a cycle ergometer will also be performed with a naso-oral mask intended to desensitize discomfort.

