**Figure 3. F3:**
[figure not shown]
Data collection timeline at the lab scheduled before allocation and repeated upon intervention completion. BP= blood pressure, v = variability, RCBA = resting carotid body activity, CPET = cardiopulmonary exercise testing.

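### The protocol gives two incompatible orders for baseline laboratory visits and allocation, so it is unclear whether week-0 BP and carotid body activity are measured before participants can know their arm

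*Protocol article*

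**What the plan says.** Two passages put the three early visits after randomisation. Section 2.2 states: "The subjects will be invited to 3 visits after randomization and 2 additional visits after completing 8 weeks of a meditation trial". The Abstract agrees: "Subjects will be invited to 3 visits after randomization and 2 additional visits after completing 8 weeks of meditation or waiting-list control". Section 2.2 then sets out what those visits contain. Visit 1 covers questionnaires, anthropometry and familiarisation. For visit 2 it says that the "visit to the lab will be dedicated to studying resting ventilatory variability (RVV), BP measurements under normoxic or hyperoxic trials conditions (NHT"), together with RCBA. Visit 3 is the exercise test with exercise ventilatory variability.

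Two further passages describe people attending visit 1 as already having an arm. Section 2.5.5 says "all randomized subjects will be invited to the laboratory to perform several normoxic BP measurements", and section 2.5.4 says "the subjects allocated to both groups will be invited to an introductory explanation of hypertension after laboratory instrument familiarization".

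Two passages give the reverse order. Section 2.4.4 says: "Once a patient signs the informed consent form and baseline data acquisition has been concluded, the study researcher will open the envelope". The Figure 3 legend reads: "Data collection timeline at the lab scheduled before allocation and repeated upon intervention completion".

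**The concern.** This is more than untidy wording, because visit 2 is the baseline for every primary outcome in section 2.6.1. The comparison is meditation against a waiting list, which cannot be hidden from participants once the arm is disclosed. Section 2.4.5 blinds participants to the hypotheses but not to their arm.

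If allocation comes first, three things are at stake:

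- Resting BP, ventilation and effort in a maximal exercise test could plausibly respond to expectation or disappointment before the intervention starts.
- Laboratory staff, who are meant to be blinded, would meet participants who may know their arm at baseline as well as at week 8.
- People who leave between allocation and visit 2 would count as randomised with no week-0 value. Section 2.1 promises an intention-to-treat analysis, and section 2.6 seeks week-8 assessments from anyone who drops out after randomisation.

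**Working it through.** The plan gives no figure to reproduce. The check is to set the passages side by side and test whether any reading reconciles them.

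**Which visits are meant.** The Abstract and section 2.2 count 3 + 2 = 5 visits. Section 2.2 says the in-laboratory physiological sequence is repeated after the 8 weeks. The two late visits therefore mirror visits 2 and 3, and the three early ones are familiarisation plus the two baseline laboratory days.

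**Order stated in each place.**

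| Place | What it fixes | Order |
|---|---|---|
| Abstract | all three early visits | after randomisation |
| 2.2 | all three early visits | after randomisation |
| 2.5.5 | visit 1 only | attendees already randomised |
| 2.5.4 | visit 1 only | attendees already allocated |
| 2.4.4 | baseline data | before the envelope is opened |
| Figure 3 legend | laboratory data | before allocation |

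Sections 2.5.4 and 2.5.5 speak directly only to visit 1. That they cover visits 2 and 3 is an inference from the visit order. The Abstract and section 2.2 cover all three visits explicitly.

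**First reconciling reading: randomisation means generating the list, allocation means opening the envelope.** Section 2.4.4 does give these steps to different researchers. But under that section a person has no arm until the next envelope in sequence is opened, so nobody could be a randomised subject at visit 1. Section 2.5.4 also uses the word for allocation itself when describing visit 1. The reading fails.

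**Second reconciling reading: baseline data in 2.4.4 means only demographics and questionnaires.** Section 2.2 collects those at visit 1, which it also places after randomisation. The Figure 3 legend refers to laboratory data. This reading fails too.

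**How a shift would propagate.** Write the effect on a change score as (week 8 − week 0) in the meditation arm minus (week 8 − week 0) in the control arm. Suppose knowing the arm moves the week-0 mean by *a* in the meditation arm and *b* in the control arm and leaves week 8 unaffected. The estimated effect then moves by −(*a* − *b*). The group-by-time term in section 2.10 carries this difference in full. The correlations in that section use (week 8 − week 0) / week 0 × 100, so a shifted baseline changes both numerator and denominator. A missing baseline makes the quantity undefined.

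The protocol gives no value for *a* or *b*, so no number follows.

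**The case against.** The strongest reply is that section 2.4.4 is the only passage that says how a participant obtains an arm, and it is clear: consent, baseline, envelope. The Figure 3 legend agrees, and section 2.1 claims concealed allocation. On that view the other passages are loose drafting and the trial is run correctly. This is quite possible, and if so no bias arises and only wording needs repair. It does not remove the contradiction, because section 2.2 is the visit schedule that staff would follow, and sections 2.5.4 and 2.5.5 fit it. Figures 1 to 3 are not reproduced in the text available and may show the intended order, but they could not undo the conflict in the prose.

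Other mitigating points stand in part. Laboratory researchers are to be blinded to assignment. The visit 1 briefing is common to both arms, with the meditation briefing held back to the first meditation session. The BP readings at visit 1 are for familiarisation and are not the outcome baseline.

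A reader might infer that baseline is in fact measured in people who know their arm. The documents do not support that. Section 2.4.5 tells subjects not to give clues about their group, which implies they know it at some stage, but it names no visit.

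A reader might also want to put a size on the bias by assuming a shift of 1 to 2 mm Hg. The answer depends wholly on that assumption and on the yardstick. Against the 5.9 mm Hg threshold in section 2.6.1 it is 1/5.9 to 2/5.9, or 17% to 34%. Against a detectable difference built from the pilot SD of 4.2 mm Hg, (2.00 + 0.85) × 4.2 × √(2/30) ≈ 3.1 mm Hg, it is 32% to 65%. That SD comes from 12 normotensive or prehypertensive people measured on two trial days, not from 8-week changes in hypertensive patients. Neither percentage should be reported as a finding.

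**Conclusion.** The contradiction is established: two passages put all three baseline visits after randomisation, two describe visit 1 attendees as already randomised or allocated, and two put baseline before allocation. No reading reconciles them.

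The consequence is conditional. If the section 2.2 order is followed and the arm is disclosed before visit 2, an arm-related shift in baseline passes in full into the comparison on every primary outcome. If the section 2.2 order is followed at all, early leavers are randomised without a baseline. If the section 2.4.4 order is followed, neither problem arises. The documents do not show which order was used or when participants learn their arm, and the size of any bias cannot be derived from them. The point still needs settling, because it concerns the week-0 value of all the primary outcomes and the protocol cannot be carried out as written.

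**What to change.** Make the order in section 2.4.4 and the Figure 3 legend the only one: consent, visits 1 to 3 with all baseline measures, then opening of the next envelope. Amend the Abstract and section 2.2 to say that the three visits precede randomisation. Amend sections 2.5.4 and 2.5.5 to refer to enrolled subjects instead of allocated or randomised ones. State when participants are told their arm.

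The study began in October 2022, so the order used may already vary. For each participant enrolled so far, record whether baseline preceded or followed allocation and when the arm was disclosed. If baseline followed allocation for some or all of them, say so, correct section 2.4.4 and the Figure 3 legend for that period, and acknowledge the possible baseline bias. Run a sensitivity analysis by order only if both orders occurred. Simply dropping those run the other way could remove most or all of the sample.

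For future participants the cost is wording and a site instruction, with no added visits, and it avoids randomising people who leave before baseline is complete. For those already enrolled, the cost is a check of dates and an honest statement of what was done.

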### 2.3. Ethical concerns and trial registration

This study was registered and approved by the Human Research Ethics Committee of our institution (CAAE number: 53122821.6.0000.0021). Individuals will be recruited through social media and banners and should agree to participate and sign an informed consent form. The study followed best practices in research and medical conduct and the recommendations of the Declaration of Helsinki. Rebec registration: Rebec RBR-55n74zm.

### 2.4. Sample details

#### 2.4.1. Diagnostic criteria for stage I hypertension.

Stage 1 HT was diagnosed based on both the last “Brazilian Guidelines of Hypertension”^[45]^ and the “2018 ESC/ESH Guidelines for the management of arterial hypertension.”^[46]^ Thus, a systolic blood pressure (SBP) between 140 to 159 mm Hg and/or diastolic blood pressure (DBP) between 90 to 99 mm Hg define stage 1 HT after carefully measuring technical recommendations.^[45]^

#### 2.4.2. Inclusion criteria.

Subjects will be enrolled in this trial if they meet the following inclusion criteria:(1)both genders.(2)age between 30 to 70 years.(3)previous physician diagnosis of primary hypertension or taking at least 1 antihypertensive medication.(4)minimum 1-year diagnosed stage 1 HT.(5)intake of antihypertensive medication unchanged for at least 2-months (see the Brief Medication Questionnaire).(6)not engaged in regular exercise programs (3 or more times per week) in the last 3 months before the study; and.(7)being able to read, speak, and understand Portuguese.

#### 2.4.3. Exclusion criteria.

Subjects will be excluded according to the following criteria:(1)subjects who did not adhere to the experimental protocol.(2)had an important comorbidity, such as heart failure ≥ NYHA I, COPD, cognitive impairment (mini-mental exam < 27 points) or psychiatric disease, previous stroke, neuromuscular disease, asthma, uncontrolled diabetes, peripheral vascular disease, obesity grade III, renal failure of stage > 2 with glomerular filtration rate < 60 mL/minutes/1.73 m2, sleep apnea, malnutrition (BMI < 18.4) or other diseases that interfere with the performance of the protocol.(3)missing more than 2 weekly based supervised meditation sessions.(4)secondary hypertension.(5)contraindications to perform a symptom-limited maximal exercise test; and.(6)regular meditation practice.

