#### 2.4.6. Sample size.

Since there are no previous studies on CB activity after meditation, our a priori sample size calculation was based on a previously cited pilot study on RCBA ^[47]^. Considering an effect size of 0.25, a minimum of 30 subjects would be necessary to detect a significant change in chemoreception based on within-group analysis. In addition, the sample size was calculated based on a pilot study. The pilot study comprised 12 normotensive/prehypertensive healthy subjects and showed a standard deviation of the mean difference for SBP ± 4.2 mm Hg, during 2 different trial days (see Supplemental Digital Content, http://links.lww.com/MD/I272), with the oscillometric method and under the same experimental conditions (normoxic, see subsection 2.5.7). Based on a repeated measure ANOVA design with 1 between-group factor (Meditators vs Control) and 2 within-groups factors (Gas type and Time), with 4 averaged BP measures [pre-normoxic (T1), pre-hyperoxic (T2), post-normoxic (T3), post-hyperoxic (T4)] for each subject, upon resting condition, 30 subjects per group would be adequate in a 2-sided study to set an error type I = 0.05 and *β* = 0.80. Considering a 20% dropout and exclusion rate, a minimum total sample size of 36 per group was required. This sample size is concordant with several studies on the effects of meditation on hypertension.^[47]^

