#### 2.5.11. Transcedental meditation (TM).

Transcendental meditation follows previously explored methods.^[58,59]^ A certified trainer will teach the TM technique to the group in the standard 4-day course preceded by an introductory briefing. The subjects will be widely informed about the method, receiving a 1-hour group-based introductory briefing about the method in the 1st session, followed by a personal interview, personal instruction session, and group verification sessions on 3 consecutive days following personal instruction. To verify the correctness of TM practice, group-based TM sessions will be performed once a week, guided by a senior professional therapist in a 20-minutes session in an appropriate and comfortable room while sitting comfortably with their eyes closed. During the week, the subjects will be trained to perform 2 20-minutes unsupervised sessions at home each day. TM will be implemented in a more cognitive fashion, with passive mental focusing associated with slow breathing. Predefined weekly contact by phone will be performed to check for adherence and adverse effects.

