### 2.6. Outcomes

For participants who dropped out of the study at any time after randomization, researchers will use contact details to encourage them to undergo the end-study outcome assessments (8-weeks). Thus, outcomes will be assessed before and after the intervention period, regardless of attending or completion status.

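### An exclusion criterion that only randomised TM participants can meet, and a second that reaches conduct after randomisation, contradict the stated intention-to-treat analysis

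*Protocol article*

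**What the plan says.** Section 2.1 describes a randomised trial "with 8 weeks of follow-up analyzed using an intention-to-treat approach". Section 2.6 supports this: people who drop out after randomisation are encouraged to attend the 8-week visit, and "outcomes will be assessed before and after the intervention period, regardless of attending or completion status".

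Section 2.4.3 sets out who will be excluded. Criterion (1) is "subjects who did not adhere to the experimental protocol" and criterion (3) is "missing more than 2 weekly based supervised meditation sessions". They stand in the same list as comorbidities, secondary hypertension and regular meditation practice, with no note that they work differently.

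The supervised sessions belong to the TM intervention: section 2.5.11 says "group-based TM sessions will be performed once a week". For controls, section 2.4.4 says "The CG will remain under pharmacological treatment for 8 weeks and will be set up on a waiting list".

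Section 2.4.6 enlarges the sample from 30 to 36 per group with the words "Considering a 20% dropout and exclusion rate". Section 2.10 gives the tests but names no analysis set.

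**The concern.** A criterion that depends on attendance during the intervention removes people who have already been randomised. Controls have nothing to attend, so criterion (3) selects in one arm only. Followed literally, it compares those TM participants who kept coming with everyone on the waiting list.

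People who keep attending may differ from those who do not in ways that also affect BP or carotid body activity. If so, the groups could differ at week 8 with no effect of TM. This touches all three primary outcomes in section 2.6.1: BP under normoxia, BP under hyperoxia, and resting carotid body activity (RCBA).

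This is not detail that an article may leave to a fuller plan. Two rules that cannot both be followed are printed in the same document. Until one gives way, the primary analysis population could be settled after attendance and outcomes are known.

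**Working it through.** **Step 1. When, and in which arm, can each criterion be met?**

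- Criterion (3): sessions start after allocation and are held only for the TM arm (2.5.11); controls wait (2.4.4). It can be met only after randomisation and only in the TM arm.
- Criterion (1): it names no time and no arm. It could cover failure with laboratory procedures at baseline, and equally non-adherence during the 8 weeks.

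**Step 2. Are exclusions treated as lost sample?** The plan's own figure reproduces as 30 × (1 + 0.20) = 36 per group. The allowance covers dropout and exclusion together, so excluded people are counted among those not available. It does not say which exclusions are meant, and it is the same in both groups although criterion (3) cannot occur in controls.

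**Step 3. How many TM participants could criterion (3) remove?** One session a week for 8 weeks is about 8 sessions, so missing more than 2 means missing at least 3. With an assumed, independent chance q of missing each session, the share removed is P(X ≥ 3), X ~ Binomial(8, q):

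| q | TM arm removed | Control arm removed |
|---|---|---|
| 10% | 3.8% | 0 |
| 15% | 10.5% | 0 |
| 20% | 20.3% | 0 |
| 25% | 32.1% | 0 |
| 30% | 44.8% | 0 |

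**Step 4. What could this do with no true effect?** Inputs: 36 per arm and SD 4.2 mm Hg for the systolic difference between two days (pilot, 2.4.6). Assumed: a share e of the TM arm is removed, being the lowest attenders, and attendance correlates r with BP change (normal model).

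- Shift in SD units = r × φ(c) / (1 − e), where c is the e-quantile of the standard normal.
- For e = 0.20: c = −0.842, φ(c) = 0.280, so the shift is r × 0.280/0.80 = 0.350r.
- Standard error in SD units: √(1/28.8 + 1/36) = √0.0625 = 0.25, because 36 × 0.80 = 28.8.
- With t = shift/0.25, type I error = 1 − Φ(1.96 − t) + Φ(−1.96 − t).

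| e | r | Shift (SD) | Shift (mm Hg) | Type I error |
|---|---|---|---|---|
| 20% | 0.1 | 0.035 | 0.15 | 5.2% |
| 20% | 0.3 | 0.105 | 0.44 | 7.0% |
| 20% | 0.5 | 0.175 | 0.73 | 10.8% |
| 10% | 0.5 | 0.097 | 0.41 | 6.9% |
| 30% | 0.5 | 0.248 | 1.04 | 16.0% |

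The size is what is tabulated; the sign follows the sign of r. The mm Hg column scales with the SD, which comes from 12 normotensive or prehypertensive people and may not fit 8-week changes in hypertensive participants. The type I error column does not depend on the SD. The calculation is a simple comparison of mean changes, not the full repeated-measures model of 2.10.

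**The case against.** The strongest defence is that the trial intends intention-to-treat and says so. Section 2.1 declares it, section 2.6 arranges to collect the data it needs, and section 2.10 never says that excluded people leave the analysis. The participant flow is in Figure 2, which cannot be seen here. A reader might infer from 2.4.3 that intention-to-treat has been abandoned. The documents do not support that: they contradict themselves. What remains is that 2.4.3 says subjects meeting these criteria will be excluded, 2.4.6 counts exclusions as losses, and nothing in the text says which rule prevails.

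A reader might also infer that both criteria can only be judged after allocation. For criterion (1) this is not established. Section 2.4.4 opens the envelope once baseline data are complete, and the Figure 3 caption places the first laboratory work before allocation, so (1) could partly be a legitimate screen. Section 2.2 points the other way, with three visits after randomisation. Criterion (1) therefore needs limiting, not necessarily deleting.

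Two further inferences go too far:

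- **That the bias must favour TM.** No section says that attenders take their drugs more reliably or are less stressed. The outcome is a change in BP, so people with less room to fall might attend more.
- **That the bias is a known fraction of the effect the trial can detect.** The plan states no detectable difference, so any such ratio would not be its own. Against the only BP threshold given, 5.9 mm Hg in 2.6.1, the illustrated 0.15 to 0.73 mm Hg is 2.5% to 12%.

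It is also fair that the study calls itself exploratory. That softens the consequence of a modest bias but does not reconcile the two rules.

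**Conclusion.** The point holds, firmly for criterion (3) and conditionally for criterion (1). Criterion (3) is a post-randomisation exclusion that can act in one arm only. Criterion (1) becomes a post-randomisation exclusion whenever it is applied to conduct after allocation. Each is incompatible with 2.1 and 2.6, and following 2.4.3 would remove the protection of randomisation from the primary BP and RCBA comparisons.

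The documents fix neither the size nor the direction. With 20% of the TM arm removed and correlations of 0.1 to 0.5, the illustration runs from almost nothing (0.15 mm Hg, type I error 5.2%) to a doubling of the false-positive rate (0.73 mm Hg, 10.8%). Removal rates and correlations are assumptions throughout. The contradiction itself rests on no number. It should be settled before attendance and outcomes are known, because a choice of analysis set made afterwards would carry little weight.

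**What to change.** - Section 2.4.3: remove criterion (3). Limit criterion (1) to failures before allocation, and reconcile 2.2 with 2.4.4 and the Figure 3 caption so that it is clear which procedures come before allocation.
- Section 2.10: state that every randomised participant is analysed in the allocated arm whatever their attendance. Use more than 2 missed supervised sessions only to define a per-protocol sensitivity set, labelled as such.
- Section 2.4.6: make the 20% allowance refer to missing outcome data (dropout) only.

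The cost is a change of wording. No extra visits are needed, because 2.6 already plans to obtain outcomes from people who stop attending. The downside is that the estimate may be slightly less favourable to TM, since it will include people who attended little.
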